## Abstract

**Background:**

With an ever-increasing elderly population, orthopaedic surgeons are faced with treating a high number of fragility fractures. Biomechanical tests have demonstrated the potential role of osteoporosis in the increased risk of fracture fixation complications, yet this has not been sufficiently proven in clinical practice. Based on this knowledge, two clinical studies were designed to investigate the influence of local bone quality on the occurrence of complications in elderly patients with distal radius and proximal humerus fractures treated by open reduction and internal fixation.

**Methods/Design:**

The studies were planned using a prospective multicentre open cohort design and included patients between 50 and 90 years of age. Distal radius and proximal humerus fractures were treated with locking compression 2.4 mm and proximal humerus internal locking plates, respectively. Follow-up examinations were planned for 6 weeks, 3 and 12 months as well as a telephone interview at 6 months. The primary outcome focuses on the occurrence of at least one local bone quality related complication. Local bone quality is determined by measuring bone mineral density and bone mineral content at the contralateral radius. Primary complications are categorised according to predefined factors directly related to the bone/fracture or the implant/surgical technique. Secondary outcomes include the documentation of soft tissue/wound or general/systemic complications, clinical assessment of range of motion, and patient-rated evaluations of upper limb function and quality of life using both objective and subjective measures.

**Discussion:**

The prospective multicentre open cohort studies will determine the value of local bone quality as measured by bone mineral density and content, and compare the quality of local bone of patients who experience a complication (cases) following surgery with that of patients who do not (controls). These measurements are novel and objective alternatives to what is currently used.

**Trial registration numbers:**

Clinical Trials.gov NCT01144208 and NCT01143675

## Background

Osteoporosis leads to rarefaction of the intrinsic bone structure [1]. Thinning of the cortical shell in combination with less and thinner trabeculae [2] leads to inferior mechanical properties, e.g. lower compression force [3]. The subsequent increased incidence of low-energy fractures is well-known [4,5]. It is also known from epidemiological studies that permanent, untreated osteoporosis significantly increases the risk for another fracture [6] and furthermore, aggravates fracture fixation. The latter has been demonstrated in a number of biomechanical experiments that assessed various implant configurations (e.g. single screws, screw-plate constructs, dynamic hip screws) at different bone locations (e.g. proximal humerus, proximal femur or vertebra) under different loading modes (e.g. quasi-static, limited cyclic) [7]. Screw pull-out is significantly associated with bone mineral density (BMD) [8] or more precisely with the minimal contact area between implant and low density bone [9]. Consequently, fixation strength should be affected by osteoporosis and a higher risk for fixation failure in the form of screw pull-out or cut-through for example, might be expected.

Despite these biomechanical findings, very few clinical studies have reported an association between osteoporosis and an increased risk of fixation failure [10,11]. A recent systematic literature review also revealed that despite strong biomechanical evidence, an association could not be reproduced in clinical studies [7]. Furthermore, two reasons for the missing link were identified: 1) the lack of appropriate local osteoporosis diagnostics, and 2) the lack of uniform definitions for complications. The first aspect seems logical since current osteoporosis diagnostic tools were developed only to predict an overall fracture risk and not the local risk of fixation failure. Eckstein et al showed a substantial heterogeneity in BMD across different measurement sites and also found that local bone strength is best predicted by site-specific measurement [12]. Thiele et al showed that locally measured bone morphometric parameters like cortical bone mass, cortical thickness and bone density can explain more than 80% of the pull-out strength at the proximal femur [13]. Seebeck et al found an increase of up to 93 and 98% considering the adjacent cortical thickness and cancellous bone density measurements along single screws, respectively [8]. All these findings demonstrate the need for appropriate local bone density/morphometry assessment to evaluate a possible association with fixation failure.

Reports on complications occurring after surgical fracture treatment are rare and usually accompanied with inconsistency. This is the main reason for the absence of a universal classification system defining complications and thereby, a lack of clinical correlation between osteoporosis and the risk of fracture fixation failure. A recent systematic literature review of orthopaedic randomised controlled trials revealed that awareness and quality of reporting are low among orthopaedic surgeons [14]. Some authors report all complications without stratification for the possible relation to the intervention, whereas others either do not observe complications or simply do not report them. Systematic complication definitions including a characterisation of their possible relation to the tested interventions are a major prerequisite for studies focusing on bone quality and fixation.

The focus of this article is to describe a protocol that was designed to examine a hypothesised association between local bone quality and the risk of fixation failure. Local bone quality is measured using an up-to-date diagnostic tool for assessing local BMD and the risk of fixation failure is derived from a final independent assessment of the number of complications related to a defined set of categorised factors, i.e. local bone, fracture, implant or the surgical application. The protocol is applied in two specific clinical studies focusing on common fracture locations often associated with osteoporosis, the distal radius and proximal humerus.

## Methods/design

### Study design

Both studies are designed as prospective, multicentre open cohort studies with a nested case-control design. Open cohorts do not select subjects according to the type of exposure variable but enrol all members of the population and determine subsequent exposure status. In this case, exposure (i.e. local BMD level) has already occurred, but is not a criterion for subject enrolment. The major advantage of this type of approach as compared to a classical case control design is that in addition to comparing the BMD in cases and controls, we can also obtain an estimate of the risk of experiencing a complication in the general population.

The studies will be conducted at several participating clinics from Austria, Germany, Switzerland, Italy, China, Singapore and the US; recruitment will take place at 11 hospitals for the distal radius and 9 for the proximal humerus studies (Table 1).

**Table 1 T1:** List of participating clinics

Clinic	Distal radius	Proximal humerus

### Identification and recruitment of study participants

Patients between and including 50 and 90 years old are eligible for a study. The main inclusion criterion is a radiologically confirmed closed distal radius or proximal humerus fracture not older than 7 or 10 days, respectively (Table 2 and 3). For proximal humerus cases, only those patients with normal age-dependent function prior to operation, a monotrauma, and fracture displacement with a segment displacement of 0.5 cm or angulation > 45° [15] except dislocated fractures of the greater and lesser tuberosity will be recruited (Table 3).

**Table 2 T2:** Eligibility criteria for the distal radius fracture group

Inclusion criteria (distal radius)
• Radiologically confirmed closed fracture (≤ 7 days) of the distal radius
• Primary fracture treatment with a volar LCP 2.4 mm
• Age > 50 and < 90 years
• Willing and able to give written informed consent to participate in the study
• Willing and able to participate in the study follow-ups according to the study protocol
• Willing and able to comply with the postoperative management program
• Able to understand and read country national language at an elementary level
**Exclusion criteria (distal radius)**
• Ulna fracture (except an associated fracture of the ulnar styloid process)*
• Open distal radius fracture
• Concomitant contralateral radius fracture
• Previous distal radius fracture on either side after the age of 25
• Time to operation > 7 days
• Polytrauma
• Regular systemic therapy with corticosteroids due to chronic disease
• Legal incompetence
• Patient received radio- or chemotherapy prior to, during or within the last year
• Currently diagnosed with active cancer
• Recent history of substance abuse (i.e. recreational drugs, alcohol)
• Prisoner
• Currently involved in a pharmaceutical clinical study**
• Has a disease process that would preclude accurate evaluation (e.g. neuromuscular or rheumatic disease, significant psychiatric or metabolic disorders)

* a) simple fractures of the ulna neck, b) multi-fragmentary fractures of the ulna neck, c) fractures of the ulna head and d) fractures of the ulna proximal to the neck are excluded, while radio-ulna dislocation (fracture of the styloid process) may be included.

** Simultaneous participation in another orthopaedic/surgical study with the same or another fracture will be approved by the principal clinical investigator

**Table 3 T3:** Eligibility criteria for the proximal humerus fracture group

Inclusion criteria (proximal humerus)
• Radiologically confirmed closed fracture (≤ 10 days) of the proximal humerus
• All dislocated (according to modified Neer*) proximal humerus fractures except dislocated fractures of the greater and lesser tuberosity
• Primary fracture treatment with a PHILOS plate
• Age ≥ 50 and ≤ 90 years
• Normal (pre-trauma) function of both shoulders according to age
• Monotrauma
• Willing and able to give written informed consent to participate in the study
• Willing and able to participate in the study follow-ups according to the study protocol
• Willing and able to comply with the postoperative management program
• Able to understand and read country national language at an elementary level
**Exclusion criteria (proximal humerus)**
• Open proximal humerus fracture
• Concomitant contralateral proximal humerus fracture
• Previous proximal humerus fracture on either side after the age of 25
• Time to operation > 10 days
• Polytrauma
• Cuff arthropathy of the contralateral proximal humerus
• Associated nerve or vessel injury
• Regular systemic therapy with corticosteroids due to chronic disease
• Legal incompetence
• Patient received radio- or chemotherapy prior to, during or within the last year
• Currently diagnosed with active cancer
• Recent history of substance abuse (i.e. recreational drugs, alcohol)
• Prisoner
• Currently involved in a pharmaceutical clinical study**
• Has a disease process that would preclude accurate evaluation (e.g. neuromuscular or rheumatic disease, significant psychiatric or metabolic disorders)

* Segment displacement > 0.5 cm or angulated > 45° [15].

** Simultaneous participation in another orthopaedic/surgical study with the same or another fracture will be approved by the principal clinical investigator

Patients with open fractures, a concomitant contralateral fracture at the same location, or a previous fracture on either side after the age of 25 years are excluded. Furthermore, patients receiving regular systemic therapy with corticosteroids due to chronic disease are excluded. For the proximal humerus study, patients are excluded as well when they had cuff arthropathy of the contralateral side or associated nerve or vessel injuries (Table 3).

### Treatment

At the distal radius, a volar 2.4 mm locking compression plate (LCP) is used for stable internal fixation with a volar approach according to Henry et al [16]. A proximal humerus interlocking (PHILOS) plate is used for primary treatment of the upper limb fracture group. Both implants (Synthes GmbH, Oberdorf, Switzerland) are applied using standard recommended surgical procedures [17,18].

### Primary outcome measure

The primary aim of both studies is to evaluate if patients who experience bone/fracture or implant/surgery complications following surgical treatment with open reduction and a fixation plate (cases) have poorer bone quality (determined by local BMD) compared to control patients who do not experience a complication; hence, whether there is an association between poor bone mineral density and the risk of complication. Therefore, the main outcome involves documentation of the occurrence of at least one local bone quality related complication during 12 months of follow-up. The classification of complications complies with the previously defined system of AO Clinical Investigation and Documentation [19]. The qualifying events include those directly involving either the local bone and fracture or the implant and its surgical application. A detailed definition of these clinical and/or radiologically detectable events for the distal radius and proximal humerus are listed in Table 4 and 5, respectively.

**Table 4 T4:** Detailed list of categorised definitions for bone/fracture and implant/surgery complications located at the distal radius

Bone/fracture	
(Secondary) Loss of reduction = secondary fragment dislocation = redisplacement = loss of radial/ulnar length = dorsal angle change = dorsal or palmar shortening	Any change in intra-/extraarticular angles, radial/ulnar length or secondary fragment dislocation compared to the immediate postoperative measurements
	
Malunion	Healed fracture in deformity (e.g. varus/valgus, rotational malunion) as a consequence of loss of reduction
Malunion = residual extraarticular deformity = residual articular gap/step-off	Inadequate/insufficient anatomical reduction as a consequence of significant change of the postoperative position. Bone unites in abnormal position and/or alignment
	
Fracture impaction	Articular impaction of ≥ 1 mm
	
Delayed healing	Insufficient signs of healing (> 3 months)
	
Nonunion	Indiscernible signs of healing (> 6 months)
Refracture = secondary fracture	Fracture occurs at the same radial site with a load level otherwise tolerated by normal bone after the bone has solidly bridged
	
Functional deficit	As assessed with the functional scores of DASH, PRWE, ROM and grip strength

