**Implant/surgery**	

Primary malpositioning of plate	Failure to fix each fragment and/or failure to implant plate according to technical guide [17] (including anatomical reduction and plate positioning) during operation
	
Primary malpositioning of screw	Screws placed into the radiocarpal or radioulnar joint as seen on oblique X-rays or incorrect screw size chosen during operation
	
Secondary screw perforation = secondary screw loosening = screw back-out	Screws displaced into the radiocarpal or radioulnar joint as seen on oblique X-rays or incorrect screw size chosen (no initial perforation)
	
Implant (plate and screw) loosening	Multiple proximal or distal screw loosening leading to firstly, relative movement between one main fragment and the plate and secondly, pull-out of the implant
	
Plate/screw failure/breakage	Plate/screw breakage
	
Radiolucency around screw	Appearance of screw on X-ray without screw loosening

DASH = Disabilities of the Arm, Shoulder and Hand questionnaire PRWE = Patient-Rated Wrist Evaluation questionnaire ROM = Range Of Motion

**Table 5 T5:** Detailed list of categorised definitions for bone/fracture and implant/surgery complications located at the proximal humerus

Bone/fracture	
(Secondary) Loss of reduction = secondary fragment displacement = redisplacement	Significant change of head position against shaft or fragment dislocation compared to the immediate postoperative position
= secondary dislocation of greater tuberosity	Relative change of greater tuberosity compared to the immediate postoperative position
	
Malunion	Fracture healed with deformity and bone unites in abnormal position and/or alignment (e.g. varus/valgus, rotational malunion)
	1. as a consequence of loss of reduction
	2. as a consequence of inadequate/insufficient anatomical reduction as observed on postoperative X-rays.
	
Delayed healing	Insufficient signs of bridging/continuous fracture line still visible up to 6 months
Nonunion	Indiscernible signs of bridging/continuous fracture line still visible after 6 months
	
Head impaction = secondary fracture impaction	Secondary impaction/sintering of the head fragment with consecutive intraarticular screw penetration due to mechanical failure (not due to avascular collapse of the head fragment) compared to immediate postoperative position
	
Head necrosis	In situ death of bone within the humeral head due to disruption of blood supply, leading to partial or complete collapse of the head
	

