### Timing of outcome assessments

For both studies, patients will be followed from the day of initial treatment to one year thereafter. The follow-up includes initial hospitalisation (baseline) and follow-up visits at 6 weeks, 3 months and 12 months following surgery. At these follow-ups all outcomes except radiological data will be measured in the hospitals. Any unplanned follow-up visits resulting from the occurrence of a complication during the 12-month period will also be documented. Additional telephone interviews will take place at the 6-month postoperative period to obtain the patient self-rating PRWE, SPADI, and EuroQol5 questionnaire evaluations.

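### Distal radius study: loss of reduction is any change from the postoperative measurement, with no minimum, so reading error alone can make a patient a case

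*Protocol article*

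**What the plan says.** The section Primary outcome measure sets the outcome as "the occurrence of at least one local bone quality related complication during 12 months of follow-up". It presents Tables 4 and 5 as the detailed definitions of the qualifying events, so the wording of each row decides who is a case.

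- **Loss of reduction, distal radius (Table 4, bone/fracture):** "Any change in intra-/extraarticular angles, radial/ulnar length or secondary fragment dislocation compared to the immediate postoperative measurements". No size of change is given.
- **Fracture impaction, distal radius (Table 4):** "Articular impaction of ≥ 1 mm". This row has a number.
- **Loss of reduction, proximal humerus (Table 5):** "Significant change of head position against shaft or fragment dislocation compared to the immediate postoperative position". This row has a qualifier but no number.
- **Radiolucency around screw, distal radius (Table 4, implant/surgery):** "Appearance of screw on X-ray without screw loosening".
- **Delayed healing:** for the humerus (Table 5), "Insufficient signs of bridging/continuous fracture line still visible up to 6 months"; for the radius (Table 4), "Insufficient signs of healing (> 3 months", a lower limit only.

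An independent radiologist first reads all films for wrist alignment and events. An independent review board makes the final classification after the 12-month follow-up. The section Sample size and statistical analysis expects cases and controls in the ratio 15:85 at the radius. There, cases are patients with a bone or fracture complication, and controls are patients with no recorded complication.

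**The concern.** Angles and radial/ulnar length are continuous readings. Two readings of a fracture that has not moved can differ, and a rule that counts every difference turns that noise into loss of reduction. The authors set a limit or a qualifier in neighbouring rows, so its absence here is a feature of the stated rule.

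The row is a bone/fracture event, so it creates cases under the outcome section and also under the narrower case definition in the analysis section. If stable fractures enter the case group, its mean BMD moves towards that of the controls and the primary comparison weakens. If the board instead chooses its own cut-off once follow-up has ended, the primary outcome is settled after the data exist. The Background names the lack of uniform complication definitions as one of two reasons why earlier clinical studies found no association, and these tables are meant to supply them.

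**Working it through.** **Inputs, all from Sample size and statistical analysis:** 200 radius patients, case share p = 0.15, BMD difference 0.03 g/cm², SD 0.05 g/cm², two-sided α = 0.05, stated power 85%, 10% added for adjustment, 10% loss to follow-up.

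**Step 1. Reproduce the plan.** There are 30 cases and 170 controls. SE = 0.05 × √(1/30 + 1/170) = 0.0099, and 0.03 / 0.0099 = 3.03. Power = Φ(3.03 − 1.96) = 85.8%, or 85.4% with the noncentral t, against 85% stated. The total is 200 × 1.1 / 0.9 = 244.4, against 244 stated. The arithmetic is sound and depends on the 15% case share.

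**Step 2. Add false positives.** Let a share f of true non-cases be labelled as cases, independently of BMD, and let all true cases be found. The article gives no value for f, so f is an assumption.

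- Labelled case share: s = p + (1 − p)f
- Proportion of labelled cases that are true: v = p / s
- Observed difference: 0.03 × v
- Variance among labelled cases: 0.05² + v(1 − v) × 0.03²
- SE² = that variance / (200s) + 0.05² / (200(1 − s))
- Power = Φ(difference / SE − 1.96)

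For f = 10%: s = 0.15 + 0.85 × 0.10 = 0.235, v = 0.15 / 0.235 = 0.638, and the difference is 0.0191. The variance is 0.0025 + 0.638 × 0.362 × 0.0009 = 0.00271. SE = √(0.00271/47 + 0.0025/153) = 0.0086. Power is about 60%.

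| f (assumed) | labelled case share | observed difference (g/cm²) | power, N = 200 |
|---|---|---|---|
| 0% | 15.0% | 0.0300 | 86% |
| 5% | 19.3% | 0.0234 | 72% |
| 10% | 23.5% | 0.0191 | 60% |
| 20% | 32.0% | 0.0141 | 44% |
| 50% | 57.5% | 0.0078 | 19% |

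**Step 3. The two other wordings.** The radiolucency row does not mention a lucent zone. As worded it fits any visible screw that is not loose. It is an implant/surgery event, so under the analysis section it would not create a case, but it could remove a patient from the controls. The humerus delayed-healing row has an upper time limit and no earliest time, while the radius row has a lower limit. Both sit next to nonunion rows that turn on 6 months.

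**The case against.** The best defence is that tables are read with their labels and with judgement. The Safety monitoring section defines a complication as a departure from normal treatment or outcome, an independent board classifies on anonymised data, and the article condenses a fuller protocol that may hold operating criteria.

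Much of this stands for the secondary items. The label of the radiolucency row shows which event is meant, so the definition is garbled and nobody is likely to code every plated wrist. The humerus wording, under the label of delayed healing, can be read as a line that persists to 6 months.

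The defence is weaker for radius loss of reduction. Calling an event a departure from normal does not say how many degrees or millimetres count, and anonymised review supplies no threshold. The row is not silent on the point: it states that every change counts.

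A reader might infer two stronger conclusions. The first is that nearly every patient in both studies is a case. That needs an assumed reading error and literal use of the radiolucency and humerus rows. It also needs a film schedule, which the text does not give; the flow chart is not shown. The second is that radius delayed healing can hardly be observed, because the plan has "follow-up visits at 6 weeks, 3 months and 12 months following surgery" and only a telephone interview at 6 months. But unplanned visits for complications are documented, and the delayed-healing and nonunion rows differ in degree as well as time. Both are bone/fracture events, so confusing them leaves case status unchanged.

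**Conclusion.** The concern holds for the distal radius study. The loss-of-reduction rule is wrong as written, because a measured quantity needs a minimum change before it can define a case. Taken literally, it undermines the 15:85 split on which the 85% power rests.

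The size is illustrative: about 60% power if 10% of true non-cases are mislabelled, and 44% if 20% are. These figures assume mislabelling unrelated to BMD, full capture of true cases, and the planned difference and SD. If some of the small changes counted are real and related to low BMD, the loss would be smaller. The sample size calculation itself is correct. The radiolucency and humerus delayed-healing wordings need correction, but they do not show that either study fails.

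**What to change.** Before the board classifies any film, and without reference to BMD:

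1. In Table 4, replace the any-change rule with a change exceeding a pre-specified threshold for each parameter. The sponsor sets each threshold above the radiologist's measurement error, for example from repeat readings of a sample of films.
2. Reword the radiolucency definition to match its row label.
3. Reconcile the humerus delayed-healing wording with the radius wording and with both nonunion rows, so that each has a clear time window. The cut-offs are for the sponsor to decide.

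The cost is edits to Tables 4 and 5, matching instructions to the board, and a small repeat-reading exercise. The downside is that real shifts below the threshold are not counted.
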